### Economic evaluation

The exact number of therapy sessions is recorded. Costs of these will be estimated using data on staff salaries, overheads and activity levels. Use of other services during the 12-month period before baseline and during the follow-up (broken down into six-month periods) is measured with the Client Service Receipt Inventory (CSRI, [61]) which asks for information on the number and duration of contacts with primary and secondary health and social care professionals, and time lost from work. Service costs are calculated by combining the service use data with standard unit costs [61,82]. Lost employment costs will be calculated by combining time off work with average wage rates. Access to medical notes is agreed. These will be used to supplement CSRI data. Given that under-reporting of service use is more likely than over-reporting, we will use the higher number of contacts with clinicians if the two sources differ. Cost-effectiveness will be assessed by combining cost data with the HRSD change score: incremental cost-effectiveness ratios will be computed to show the extra cost incurred to achieve a one-unit improvement on the HRSD; uncertainty around these estimates will be addressed using cost-effectiveness planes. These analyses will be conducted first for healthcare costs and then for total costs (i.e. use of other services and lost employment). Sensitivity analyses will be conducted by increasing/decreasing the therapy costs by 25% and by using minimum wage rates to value lost employment.

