### The analysis of data

To preserve neutrality, no data will be analysed until all subjects have reached the six month follow-up point. An intention-to-treat analysis will be performed in the first instance (i.e. analysing all available data from randomised participants) using for all analyses the STATA, version 11.0 package. The numbers and percentages of losses to follow-up at 12, 18, and 24 months after randomisation will be reported and will be compared between the treatment arms with absolute risk differences (95% CIs). Any deaths and their causes will be separately reported. To increase the power and precision of the estimated treatment effect, missing baseline covariates will be imputed for our main analysis using either mean or regression imputation [77]. All available results will be used without missing outcomes being imputed. Primary analyses will be based on the assumption of ignorable drop-outs. In secondary analyses, missing values will be replaced by multiple imputations using Markoff Chain Monte Carlo methods [78].

For continuous outcome variables, the differences in mean score between those randomised to either arm of the trial will be examined using analysis of covariance adjusting by 1) baseline value of outcome 2) baseline value of the outcome, gender and age. The assumption of linearity will be assessed by residual analysis; if necessary, bootstrapping techniques will be employed. Sensitivity analyses will be conducted to take into account missing data using multiple imputation, which assumes data are 'missing at random'. For continuous response variables, statistical analyses will be based on linear mixed models [79].

For binary responses, mixed-model logistic regression models and generalized estimating equations will be used [80]. Logistic regression will be used to compare proportions of patients that have lost their diagnosis during the treatment and follow-up period in the two groups using an HRSD of 14 as criterion. Analysis of 'time to first recovery' and ‘time to first relapse’ outcome will also be conducted using survival analysis methods and the log-rank test for bivariate comparisons and Cox's proportional hazards to adjust for gender, stratification variables and time spent on treatment prior to randomisation. The dependencies between design points in the case of linear mixed models will be accounted for by assuming an unstructured correlation structure.

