Statistical significance will be tested with the Wald test, and CIs will be established by the Delta method [81]. Time will be handled as a categorical variable with five possible values - 0, 6, 12, 18, 24 months. The basic model will include the main effects of time, of treatment group, of the difference between theoretical and realised date of measurement and first order interaction of time and treatment. A complete model will include potential confounding factors (e.g. age group, gender etc). Complementary analyses will be carried out adjusting for the baseline level of outcome measures. 'As treated' models will be carried out by including variables describing compliance (e.g. waiting time from randomisation to initiation, degree of participation, including an indicator whether the patient received the study treatment) and auxiliary treatments such as medication.

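### The cost-effectiveness ratio is built on an HRSD change score with no baseline adjustment mentioned; taking the baseline-adjusted HRSD difference would be more precise at no cost (minor)

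*Protocol article*

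**What the plan says.** The Economic evaluation section fixes the effect measure: "Cost-effectiveness will be assessed by combining cost data with the HRSD change score". It then gives the unit: "incremental cost-effectiveness ratios will be computed to show the extra cost incurred to achieve a one-unit improvement on the HRSD". It names no model and no covariate for that effect, and does not link it to an efficacy analysis. It does say that service use over the 12 months before baseline is recorded.

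The analysis of data describes two approaches to continuous outcomes. One compares mean scores by "analysis of covariance adjusting by 1) baseline value of outcome 2) baseline value of the outcome, gender and age". The other is introduced with "For continuous response variables, statistical analyses will be based on linear mixed models". For the mixed model, "Time will be handled as a categorical variable with five possible values - 0, 6, 12, 18, 24 months", so baseline is one of the modelled occasions. The basic model contains time, group, deviation from the scheduled date and the "first order interaction of time and treatment". It has no baseline covariate, and adjustment is added later: "Complementary analyses will be carried out adjusting for the baseline level of outcome measures".

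Under Randomisation, severity is balanced by minimisation on BDI-II band (21–39 or 40+), not on the HRSD.

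**The concern.** On its plain meaning, a change score is follow-up minus baseline. Comparing its mean between arms subtracts the whole baseline difference, which fixes the regression slope of follow-up on baseline at 1. ANCOVA estimates that slope from the data. Where the slope is below 1, the change score over-corrects for chance baseline differences and carries more noise.

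The HRSD difference is the denominator of the ICER, so extra noise or a shift there passes into the cost per HRSD point and widens the scatter on the cost-effectiveness plane along the effect axis. A reader could also meet one HRSD difference in the efficacy results and a somewhat different one beneath the ICER. The analysis section itself justifies imputing missing baseline covariates by the gain in power and precision. The economic section, as worded, does not claim that gain.

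**Working it through.** The plan states no figure for this point, so there is none to reproduce.

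**Inputs.**
- From the article: 129 participants (limitations section) and 67 in the PPD arm (typology sub-study), hence 129 − 67 = 62 in TAU.
- Assumed, because the article does not give them: correlation r between baseline and follow-up HRSD of 0.2 to 0.7; equal SDs at both occasions; for illustration only, an HRSD SD of 5 and an ANCOVA effect of 3 points.

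**Step 1: precision.** With equal SDs, the variance of the between-arm difference is proportional to 2(1 − r) for an unadjusted change score and to 1 − r² for ANCOVA. The ratio is 2(1 − r)/(1 − r²) = 2/(1 + r).

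| r | Variance ratio | SE ratio | Shift per 1-point baseline imbalance (1 − r) |
|---|---|---|---|
| 0.2 | 1.67 | 1.29 | 0.8 |
| 0.3 | 1.54 | 1.24 | 0.7 |
| 0.5 | 1.33 | 1.15 | 0.5 |
| 0.7 | 1.18 | 1.08 | 0.3 |

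**Step 2: simulation.** With 67 v 62 participants, a true effect of −0.50 SD and 5,000 runs per value of r, both estimators averaged about −0.50. Empirical SEs, ANCOVA v change score, were 0.171 v 0.209 (r = 0.3), 0.153 v 0.177 (r = 0.5) and 0.128 v 0.137 (r = 0.7). The target is the same and the precision differs, in line with the formula.

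**Step 3: chance imbalance.** The two estimates differ by (1 − slope) × baseline difference, and with equal SDs the slope is r. Under simple randomisation the SE of the baseline difference is √(1/67 + 1/62) = 0.176 SD. With an SD of 5 this is 0.88 point, so a 1-point imbalance is 1/0.88 ≈ 1.1 SE.

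**Step 4: illustration for the ICER.** Hold incremental cost fixed, take an ANCOVA effect of 3 points and a 1-point imbalance in either direction.
- r = 0.2: denominator 2.2 or 3.8. 3/2.2 = 1.36 and 3/3.8 = 0.79, so the ICER changes by +36% or −21%.
- r = 0.5: denominator 2.5 or 3.5. The ICER changes by +20% or −14%.
- r = 0.7: denominator 2.7 or 3.3. 3/2.7 = 1.11 and 3/3.3 = 0.91, so the ICER changes by +11% or −9%.

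**Step 5: two equivalences.**
- A change score analysed with baseline as covariate gave the same treatment effect as ANCOVA in every simulated trial (largest discrepancy about 1e-15).
- In the basic mixed model with time 0 in the outcome, two occasions and complete data, the time-by-treatment estimate equalled the difference in mean change (−0.7929 for both in one data set). With five occasions, a date covariate and drop-out, the two need not agree exactly.

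**The case against.** A reader might infer that the economic section prescribes a raw change score in contradiction to the efficacy analysis. The document does not support that.

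- It never says raw or unadjusted. A change score with baseline as covariate is ANCOVA under another name, and a condensed article may leave covariates to a fuller plan.
- The efficacy analysis is not uniformly baseline-adjusted either. The basic mixed model gives a change-type contrast, with baseline adjustment only complementary, so one planned efficacy model already comes close to what the economic section names.

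A reader might also infer that the ICER rests on a different effect. Under randomisation both estimators are unbiased for the same mean difference, so this is a matter of efficiency.

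The sizes rest on assumptions. At r = 0.7 the SE penalty is only 8%. If HRSD scores spread out after entry, the slope exceeds r and the penalty shrinks. A slope well below 1 cannot be derived from the article: entry requires HRSD of at least 14 or BDI-II of at least 21, so HRSD is not strictly truncated. Minimisation on BDI-II band should reduce HRSD imbalance somewhat. The uncertainty of the ICER also depends on cost variance, which cannot be computed here.

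All of this stands, and it limits the point. What remains is that the section names a specific effect measure whose ordinary reading is unadjusted, and gives no sign that the baseline adjustment planned elsewhere applies to it.

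**Conclusion.** The point holds as a minor one. As plainly read, the ICER uses a valid but less efficient estimator of the HRSD difference, and one more exposed to chance baseline imbalance. For assumed r of 0.2 to 0.7 and equal SDs, the cost is an SE about 29% to 8% larger, and a shift of 0.8 to 0.3 point per point of baseline imbalance relative to ANCOVA. The percentage changes in the ICER are illustrations that further depend on the assumed 3-point effect and 1-point imbalance. Neither a bias nor a contradiction between the efficacy and economic analyses is shown. The result affected is secondary.

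**What to change.** In Economic evaluation, replace the HRSD change score with the between-arm HRSD difference adjusted for baseline HRSD. Name the ANCOVA in The analysis of data as its source or, equivalently, the change score analysed with baseline HRSD as covariate. A reference only to the efficacy model would not settle it, because that section lists several. State also that incremental cost is adjusted for service cost in the 12 months before baseline. The cost is one or two sentences; the baseline HRSD and the pre-baseline service use are already collected.

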## Qualitative & psychoanalytic case-study evaluation

### The private theories of participant and therapist

The Private Theories Interview (PTI, [83]) has been used in the investigation of patients’ views of illness and treatment response [84-86]. The imposition of the researcher’s constructions is minimised to permit the interviewee’s views to emerge. Here, we use this semi-structured interview to collect narrative material relevant to participants’ theories about their depression, their experience of treatment and of participation in a long-term, randomised trial such as this. This is done with a purposive sub-sample drawn from both patient groups and in the case of the PPD arm, with the corresponding therapists. The sample will also be matched for age, sex, demographics and treatment-response (completers versus drop-outs; and responders, intermediate or non-responders). Analysis is systematic and follows a coding manual [83] organised around the phenomenological principles of “categorization of meaning” and “concentration on meaning” [87]. Subsequent analyses will be concerned with the subject’s perspective on any therapeutic change and any associations between participants’ views and the quantitative outcome measures.

### The Tavistock psychodynamic interview (TPI)

The TPI is a specially designed instrument [88] administered by a trained psychoanalytic clinician. It draws on well validated psychodynamic and attachment-based interviews. These are the Adult Attachment Interview (AAI; [2]), the Current Relationships Interview (CRI; [89]), and the Quality of Object Relating Scale (QORS; [90]). The AAI [91], is based upon the way that the formal quality of adult discourse has been found to be lawfully related to attachment patterns established in early development. There is strong evidence for thematic continuity between narratives, dreams, early autobiographical memories and attachment patterns [92]. The CRI and the QORS both aim to assess the quality of object relationships and have been shown to have good validity [93].

The interview is carried out at the subject’s entry to the trial (TDI-Initial) and repeated two years later (i.e. six months after the end of therapy in the case of patients in the PPD condition). In addition to the clinical and personality assessment functions already described, the TPI collects narrative data about subjects' relationship histories. Particular attention is paid to key developmental and transitional phases in early childhood, adolescence, adulthood. Subjects are asked to relate a recent dream and their earliest memory. The aim is to capture subjects’ representations of key interpersonal relationships along with psychodynamically important aspects of cognitive and emotional processing, to arrive at an independent psychodynamic formulation of the subject’s illness.

The end version of the TDI looks for changes in the psychological and interpersonal functions which according to psychoanalytic thinking play a part in depressive disorders. Any changes in personal narratives or in functioning across the domains of early and later relationships, work, physical health, etc. are noted. The initial interview’s request for a recent dream and an earliest childhood memory is repeated verbatim to compare participants’ responses at the different time points. Independent judges will then categorise subjects as responders, intermediate or non-responders in terms of these psychodynamic variables. This categorisation will then be correlated with treatment allocation and quantitative outcome data. Case vignettes will delineate prototypes to examine the possibility of different constellations of illness, types of vulnerability and different patterns of responsiveness/non-responsiveness.

### Psychoanalytic case-study methods

Here we detail three sub-studies based on psychoanalytic theory, and which use case-study methods. They are designed to provide a general model which may help explain the RCT findings, and to probe specific questions.

#### A psychoanalytic typology of different forms of chronic depression

Applying the ideas of Rosenfeld [94], Blatt [95], Blatt & Zuroff [96] and Bleichmar [97], along with the preliminary clinical investigation of five pilot cases, a provisional typology consisting of seven components/dimensions has been constructed [98,99]. A purposive sub-sample drawn from the patients in the PPD arm (N = 67) will be selected by members of the clinical research workshops to include the full range of the most frequently encountered sub-forms of TRD, plus any exceptions, extreme types or others thought to be especially informative [100,101]. It will contain a minimum of 25 cases. On the basis of extended clinical discussions of therapists’ verbal session reports over the course of the subjects’ treatments, plus transcripts of audio-recordings, an evaluating group of therapists will assess the model’s fit, and its ability to make sense of the heterogeneity in the sample. Each subject will then be described along with a proforma ‘rating’ based upon the typology. The research group’s consensus and description will be checked against the therapist’s judgement, and if necessary will be modified by it (see [102,103]). The original accounts of the sub-set and the typology descriptions will be compared and checked against the therapists’ experience of the whole PPD sample. Any modifications of the model which seem to be required will then be set out. The aim throughout will be to provide ‘thick descriptions’, each of which will be referenced to the different kinds of information used.

#### The nature of change or non-change in PPD treated patients

Using a similar approach a subset of the PPD arm will be selected to include a full range of outcome categories - responders, non-responders, intermediate and treatment failures - determined on the basis of therapists’ clinical judgements. Therapists will then provide ‘thick descriptions’, again referenced to the information used, to detail the elements of the positive or negative change occurring. These descriptions will be employed with the quantitative findings and the TPI to triangulate a more three-dimensional picture of different outcomes.

#### Investigating the possible role of an increased sense of personal agency in PPD responders, and of persisting passivity in non-responders

There is evidence that a sense of personal agency [104], as one part of the executive function of the personality [105] plays an important part in mental health [106,107], in developmental or social resilience [108], and in recovery from mental disorder. In the case of depression, variations in psychosocial functionality correlate poorly with symptom severity and variations in motivation cannot be accounted for on the basis of mood alone. Psychoanalytic findings suggest that persistent forms of passivity, which may also be encountered in subjects with TRD, may militate against treatment response [109,110]. In this part of the qualitative study, the therapist selected sample of responders, non-responders, intermediate and treatment failures described above will be evaluated in terms of a psychoanalytic conceptualisation of personal agency devised by [name] & [name] (2008, unpublished).

### Ethical approval

The trial received ethical approval from the NHS West Midlands Research Ethics Committee on 28 May 2002 – reference number MREC02/07/035. Amendments were approved in July 2005, October 2009, and February 2010. Some of the ethical issues encountered in the conduct of this long-term trial are considered in the Discussion below.

Trial progress and participant recruitment. See: (Additional file 1: Figure S1).

## Discussion

This pragmatic RCT is notable in that through a high-quality design it evaluates a previously under-researched treatment, namely medium to long-term psychoanalytic psychotherapy, which aims to reduce the underlying vulnerability to depression in people suffering from a particularly complex and enduring form of this disorder. Currently, there is only one trial with a group of patients of a roughly comparable complexity [111-114]. A positive finding in our trial would significantly improve the options available for patients with this expensive and relatively poorly-served condition, which also represents a considerable burden worldwide [60,115].

However, as we have argued, the features of both the disorder and the treatment strain the limits of methodology in classical randomised clinical trials. We decided that the trial should be ecological, namely that it ought to offer information about the actual outcome over the medium to long-term of a clinically significant patient sample in the NHS. Many of the trial’s design choices followed from this decision. In this section, we discuss how we have tried to mitigate some of the strains, and list some inevitable limitations.

### The patient sample

In relation to the diagnosis of depressive and other common mental disorders, we do not yet know how to carve nature at the joints. If our study were to meet its primary requirement of ecological validity, the sample selected had to involve the fewest possible assumptions. We therefore defined the sample operationally, and included participants with co-morbid Axis I and II disorders as well as problems with physical health. Inevitably, this leads to a heterogeneous sample that includes many unknown variations capable of affecting both outcome and the interpretation of findings. Although PPD has the advantage as a treatment of being adaptable to each individual’s psychopathology, we still expect a large amount of residual variation in responsiveness amongst different patients. The treatment under test will help some participants more than others, and these variations may cancel each other out [116]. In this context, examining mean outcomes, for example, will be insufficient, and while modelling trajectories of outcomes using mixed-effects growth curves allows for differential treatment responses to be investigated, this is only possible when the critical moderators involved first have been identified and then measured. In the absence of predictions derived from well-founded theories of pathology, this is a hit or miss way of proceeding. The poor performance of outcome research in answering the question “what works for whom?” suggests that this approach might be misconceived [117]. It may be necessary to be able to drill down through group data to discover what may be deeper structures in the individual in order to understand the basis of differential degrees of responsiveness/non-responsiveness. Thus we have collected qualitative data using both psychoanalytic and phenomenological methods.

### The treatment as usual condition

A TAU control condition was chosen because it is an ecologically sound comparison group. TAU control conditions have been widely used in outcome trials, although their rationale, and what any given TAU condition may involve, has varied from case to case [25]. Our TAU control condition is only partly determined by the management protocols for these patients specified in NICE guidelines. In actual practice, there are widespread variations in the mental health resources available in different locations (NHS Atlas) and, in our experience, these are especially marked in the treatment that TRD patients receive. Some may receive exemplary care through their GPs, including social support, community mental health teams, brief counselling, and pharmacological and psychological interventions of appropriate types, durations and intensities. Others may get little if any help beyond token pharmacological treatment, with little case management. Some, perhaps following many failed attempts at treatment, may have withdrawn from all treatment endeavours. They feel they have exhausted all treatment possibilities and end up quite seriously neglected and deprived. As we have also suggested, certain characteristic features of psychosocial functioning may be integral to the TRD disorder. By adversely affecting important help-seeking behaviours, these actively exert negative effects on service provisions. These considerations lend weight to the decision to study this naturally occurring control and comparison condition [118].

A long-term trial involving patients with severe depressive disorders operates against a background of a continuous level of chronic suicidal risk punctuated by exacerbations and crises. Our guiding principle is that the TAU participant’s clinical needs must always come first. The senior research clinician and the trial’s clinical director explicitly assume responsibility for participants’ safety and have the authority to intervene and mediate in a participant’s care. In most instances this does not conflict with one of the needs of research - for instance, to keep as many subjects in the trial as possible for as long as possible. However, it follows that the trial’s TAU condition is not always and not only Treatment As Usual. Moreover, the consistent, reliable contact involved in the researcher’s administration of research measures necessarily functions like a low-intensity, psychodynamically informed supportive intervention.

